## Objectives

The primary research objective is to compare the effects of AV node ablation and AF ablation on echocardiographic and symptomatic outcomes in patients with CRT and suboptimal (<95%) biventricular pacing. The principal hypothesis tested will be that AF ablation is superior to AV node ablation in improving LV ejection fraction (primary endpoint). Secondary endpoints will include changes in LV ejection fraction and LV end-systolic volume at 1 week; and changes in LV end-systolic volume, Minnesota Living with Heart Failure Questionnaire Score, NYHA class, 6-minute walk test, NT-proBNP, AF burden, biventricular pacing percentage, ventricular arrhythmias, and inappropriate ICD shocks at 6 months. Procedural complications will be recorded, and exploratory safety outcome differences will be analyzed.

If there is no overall benefit for AF ablation on intention-to-treat analysis, it is important to determine if this is because restoring sinus rhythm has no benefit over rate control, or if the benefits of AF ablation are diluted by a high rate of recurrence. We will therefore perform a subanalysis comparing the clinical endpoints between patients who underwent AF ablation and are in sinus rhythm at 6 months, vs those who underwent AF ablation and are in AF at 6 months, vs those who underwent AV node ablation. If significant benefits are observed for patients who maintain sinus rhythm after AF ablation, the next research objective will be to determine which baseline factors are most useful to predict the chance of success after AF ablation in this patient cohort. Baseline factors tested will include clinical factors (eg, duration of AF, paroxysmal vs persistent AF, age, comorbidities) and imaging characteristics on echocardiography (eg, LV size, LV function, left atrial size). We will also assess if improvement in LV ejection fraction correlates with a reduction in AF burden.

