### Trial design

Seventy patients with existing CRT devices (implanted for dyssynchronous heart failure) and suboptimal (<95%) biventricular pacing due to AF will be included in the study. Patients will be randomized to either AV node ablation or AF ablation in a 1:1 ratio and will be followed up at 6 months.

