### Sample size justification

Previous comparisons between AV node ablation and AF ablation in patients with AF and heart failure (not indicated for CRT) found a -1% change in LV ejection fraction with AV node ablation compared to 8% with AF ablation.^26^ Measurements of changes in ejection fraction in CRT patients receiving AV node ablation or AF ablation have a variability of 7.1%–10.7%,^25^^,^^28^ giving a maximum variability of 11%. Assuming a normal distribution, a group size of 32 for each arm would achieve 90% power to reject the null hypothesis of equal means, with an alpha value of 0.05 to detect the 9% difference in change in LV ejection fraction using a 2-sided independent *t* test. This sample size will also ensure satisfactory 80% statistical power for detection of 7.5% difference in change in LV ejection fraction. To allow for an approximately 10% drop-out rate we will recruit a total of 70 patients.

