### Statistical analysis

Changes in all cardiac metrics between arms will be compared using *t* tests for independent samples. An intention-to-treat analysis will be performed for the primary and secondary endpoints. Subgroup analyses will be performed for important covariates, including heart failure etiology, sex, age, paroxysmal vs persistent AF, and duration of AF. Subsequently, prediction of outcomes will be performed using regression analyses, considering potential confounders and/or mediators. This procedure will have 2 steps. First, we will conduct exploratory analyses through the use of univariate models and graphical checks of pattern between each candidate predictor and outcome variable. On the basis of these results, and after checking that linearity assumptions are correct, we will examine multivariable associations, taking account of potential confounding factors. Predictors in univariate analysis with *P* < .10 will be further tested in a prespecified multivariable regression model. Predictors will be entered into the model in groups determined by time ordering and/or their clinical relevancy. *P* < .05 will be considered statistically significant.

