If the trial shows no significant difference between the 2 ablation strategies, it will be important to determine if this is because there is no additional benefit for AF ablation over AV node ablation, or if the clinical benefit is diminished by a high rate of AF recurrence. Success rates after AF ablation in randomized studies of heart failure patients vary from 50% to 88%.^30^ Furthermore, an international multicenter registry demonstrated that the presence of heart failure reduces success rates after AF ablation in patients with persistent AF (57.3% vs 75.8%), though the equivalent effect for patients with paroxysmal AF was marginal and not statistically significant (78.7% vs 85.7%).^31^ If patients in the AF ablation arm who maintain sinus rhythm at 6-month follow-up display superior echocardiographic remodeling and symptomatic response compared to the AV node ablation group, this will suggest a potential benefit for AF ablation in a select group of patients who have a low risk of AF recurrence after ablation. This would justify further study with a randomized trial focused on this select patient cohort. A variety of factors are known to affect the risk of recurrence after AF ablation in patients with heart failure, including patient age, duration of AF, comorbidities, and structural and electrical left atrial remodeling.^30^ Subanalyses of the RHYTHMIC study provide additional information on which factors predict outcome after AF ablation in patients with CRT devices. We recognize that patient numbers may limit the statistical power to predict outcomes; however, this study may still provide useful hypothesis-generating data to guide the design of larger trials.

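### The predictor model is called prespecified, but its terms are chosen by a univariate P<.10 screen on the same data; for AF-ablation success that means about 32 patients and few recurrences, so the results are prone to optimism

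*Protocol article*

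**What the plan says.** The Statistical analysis section of the protocol article sets out two steps for predicting outcomes. Univariate models and graphical checks come first, and the multivariable work is to be based on their results. Predictors with univariate P<.10 then "will be further tested in a prespecified multivariable regression model", entered in groups by temporal order or clinical relevance, with P<.05 as the level of significance.

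The Objectives section gives one use of this procedure. If patients who keep sinus rhythm after AF ablation show significant benefit, the next aim is to "determine which baseline factors are most useful to predict the chance of success after AF ablation in this patient cohort". It lists four clinical examples (AF duration, AF type, age, comorbidities) and three echocardiographic ones (LV size, LV function, left atrial size). The list is open, and comorbidities may be several variables.

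On size, the Sample size justification says "a group size of 32 for each arm would achieve 90% power to reject the null hypothesis of equal means" and "To allow for an approximately 10% drop-out rate we will recruit a total of 70 patients". The Trial design section says "Patients will be randomized to either AV node ablation or AF ablation in a 1:1 ratio". The Discussion adds a caveat: "We recognize that patient numbers may limit the statistical power to predict outcomes". It describes the output as hypothesis-generating.

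**The concern.** A set of terms that depends on P values from the trial data cannot be known before the data are seen. The order in which groups are entered may be fixed in advance, but the membership of the model is not. A reader who takes the word prespecified at face value will read the final P values and coefficients as if no selection had taken place.

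Screening and refitting on the same data keeps the variables whose estimates happened to be large, so the retained coefficients tend to be exaggerated and the P values too small. A real predictor masked by another in univariate analysis is dropped. The effect is strongest when events are few relative to candidates, as they are for AF-ablation success. At stake is the credibility of a list of predictors that may inform later work. The randomized comparison is not at stake.

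**Working it through.** **1. The plan's own sample size.** The inputs are a 9-point difference in LVEF change, two-sided alpha 0.05, 90% power ("with an alpha value of 0.05 to detect the 9% difference in change in LV ejection fraction using a 2-sided independent" t test) and an SD of 11 ("giving a maximum variability of 11"%). By the normal approximation, n per arm = 2(1.960 + 1.282)² × 11² / 9² = 2 × 10.51 × 121/81 = 31.4, so 32. The noncentral t distribution gives 33, with 89.6% power at 32. The stated 32 is reproduced. Seventy recruited with 10% loss leaves 63, or 31.5 per arm. The article gives no sample size or event count for the prediction model.

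**2. Patients and recurrences.** Success after AF ablation can be modelled only in the AF ablation arm, about 32 evaluable patients. Recurrences = 32 × (1 − success rate), with the rates quoted in the Discussion:

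| Source in the Discussion | Success | Recurrences |
|---|---|---|
| Randomized heart failure studies, low end | 50% | 16.0 |
| Registry, heart failure with persistent AF | 57.3% | 13.7 |
| Registry, heart failure with paroxysmal AF | 78.7% | 6.8 |
| Randomized heart failure studies, high end | 88% | 3.8 |

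That is 7–14 from the registry rates and 4–16 over the whole range.

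**3. Events per candidate.** Seven candidates are named (4 + 3). The ratio is 7/7 = 1.0 to 14/7 = 2.0, or 4/7 = 0.6 to 16/7 = 2.3 over the wider range.

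**4. Nominal behaviour of the screen.** With k independent noise candidates, P(at least one passes) = 1 − 0.9^k: 52% for k = 7 and 65% for k = 10.

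**5. Simulation of the stated procedure.** Each setting used 2,000 runs of 32 patients with independent continuous noise predictors, a univariate logistic Wald screen at P<.10, and then a joint refit of the survivors.

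| Recurrences | Candidates | At least one passes | At least one P<.05 in refit | Mean apparent AUC when any passes (truth 0.50) |
|---|---|---|---|---|
| 4 | 7 | 43.8% | 9.3% | 0.84 |
| 7 | 7 | 47.2% | 19.2% | 0.78 |
| 14 | 7 | 47.4% | 22.5% | 0.74 |
| 16 | 7 | 48.5% | 22.3% | 0.73 |
| 7 | 10 | 60.0% | 23.7% | 0.79 |
| 14 | 10 | 62.0% | 28.0% | 0.75 |

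A separate run of the 7-candidate setting at 7–14 recurrences gave 44–46%, 19–23% and 0.75–0.79.

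**6. What selection does to the reported P values.** With 7 candidates, among noise trials in which something passes, the share showing P<.05 in the refit is 19.2/47.2 = 41% at 7 recurrences and 22.5/47.4 = 47% at 14. A final-model P value below .05 is therefore weak evidence once the screen has been applied.

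**7. Comparison with a fixed set.** With three noise predictors fixed in advance, 10–13% of runs reached P<.05 for at least one (nominal 1 − 0.95³ = 14%), and the apparent AUC was 0.66–0.70. Part of this gain comes simply from testing fewer variables. The AUC is still well above 0.50, so fixing the set does not remove the need for optimism correction.

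**The case against.** The strongest reply is that this is a conditional analysis whose first step is called exploratory, in an article that concedes small numbers and calls the output hypothesis-generating. That stands as to weight. It does not settle the point: the concession is about power, meaning predictors that are missed, whereas the screen also produces false or exaggerated ones.

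Several stronger readings are tempting, and the documents do not support them.

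- *The plan will produce false predictors.* The figures are risks under a worst case in which every candidate is noise. The Discussion cites age, AF duration, comorbidities and left atrial remodeling as known to affect recurrence.
- *The 20% figure shows a fourfold inflation of the 5% level.* It is the chance of any hit among seven. Seven independent unscreened tests at exactly .05 would give 1 − 0.95⁷ = 30%. The screen's own harm lies in how the retained terms are then reported.
- *The model has 7–14 events.* The article states no count. The range 4–16 is equally consistent with it, and the permitted re-do ablation could lower the number.
- *The event limit applies to every prediction model.* The Statistical analysis section speaks of outcomes in general. A continuous outcome would not meet that limit, although screening and refitting would still bias the result.
- *A later trial would be sent to the wrong patients.* The Discussion rests the case for that trial on the sinus-rhythm subanalysis, not on this model, so such harm is speculative.
- *Validation has been left out.* The article promises no AUC, and such detail may sit in a full protocol or analysis plan that is not shown.

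The word prespecified might be meant only for the model form and the order of entry. If so, the sentence still misleads, because the terms themselves are chosen by P value.

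**Conclusion.** The point holds as a defect in a stated rule. Selection by univariate P<.10 followed by a refit on the same data is incompatible with calling the model prespecified, and it makes coefficients, P values and apparent fit prone to optimism. For AF-ablation success the setting is unfavourable: about 32 patients, an inferred 4–16 recurrences and at least 7 candidates. If all 7 were noise, about 45–50% of trials would pass at least one, and about 20% would report at least one at P<.05 for 7–16 recurrences, falling to about 9% at 4.

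These sizes assume independent continuous predictors, a logistic model and a global null. The AUC figures illustrate optimism and do not describe a planned report. The analysis is secondary, conditional and exploratory, and the primary endpoint is untouched. It is worth correcting because correction costs almost nothing.

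**What to change.** Drop the P<.10 screen. Name two or three predictors in advance from those already listed, for example AF type, AF duration and left atrial size, and enter them all regardless of univariate P. For a binary outcome use penalized fitting (Firth or ridge). Report any accuracy measure with bootstrap optimism correction. Present the remaining candidates as univariate estimates with confidence intervals, labelled exploratory. Device-recorded AF burden as a continuous outcome is an optional addition that avoids the event-count limit.

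This is a change of wording in the analysis plan and uses data already being collected. The downside is that fewer factors receive a multivariable estimate. If the investigators prefer to keep the screen, the minimum is to delete the word prespecified and label the model exploratory.

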## Discussion

At present there are no randomized studies comparing AV node ablation and AF ablation in patients with CRT and AF. RHYTHMIC is therefore an important trial that will help address a frequently encountered clinical scenario. Large observational trials support the use of AV node ablation in patients with CRT and AF,^5^^,^^22^ and this is reflected in current clinical guidance.^29^ The role for AF ablation in patients with heart failure is increasingly recognized, though its use in patients with CRT has not been widely studied. Although both AV node ablation and AF ablation are likely to increase biventricular pacing percentage, AF ablation may have the additional benefit of restoring AV synchrony. If the RHYTHMIC study demonstrates clinical superiority for AF ablation over AV node ablation, this will be an important hypothesis-generating result that will justify larger randomized studies with robust morbidity and mortality endpoints.

If the trial shows no significant difference between the 2 ablation strategies, it will be important to determine if this is because there is no additional benefit for AF ablation over AV node ablation, or if the clinical benefit is diminished by a high rate of AF recurrence. Success rates after AF ablation in randomized studies of heart failure patients vary from 50% to 88%.^30^ Furthermore, an international multicenter registry demonstrated that the presence of heart failure reduces success rates after AF ablation in patients with persistent AF (57.3% vs 75.8%), though the equivalent effect for patients with paroxysmal AF was marginal and not statistically significant (78.7% vs 85.7%).^31^ If patients in the AF ablation arm who maintain sinus rhythm at 6-month follow-up display superior echocardiographic remodeling and symptomatic response compared to the AV node ablation group, this will suggest a potential benefit for AF ablation in a select group of patients who have a low risk of AF recurrence after ablation. This would justify further study with a randomized trial focused on this select patient cohort. A variety of factors are known to affect the risk of recurrence after AF ablation in patients with heart failure, including patient age, duration of AF, comorbidities, and structural and electrical left atrial remodeling.^30^ Subanalyses of the RHYTHMIC study provide additional information on which factors predict outcome after AF ablation in patients with CRT devices. We recognize that patient numbers may limit the statistical power to predict outcomes; however, this study may still provide useful hypothesis-generating data to guide the design of larger trials.

The definition of “success” for AF ablation varies between studies and is often related to recurrence of a >30-second episode of atrial arrhythmia during the follow-up period.^32^ Given that all enrolled patients have CRT devices in situ, the RHYTHMIC study has the advantage of allowing continuous rhythm monitoring after ablation, and therefore the effect of ablation on AF burden can be determined. In a recent study of 207 patients with AF and existing pacemakers, ICDs, or implantable loop recorders, AF ablation significantly reduced the burden of AF in patients with both paroxysmal and persistent AF at 1-year follow-up (median AF burden 1.05% vs 0.10% and 99.9% vs 0.30%, respectively).^33^ Significant reductions compared to pre ablation were also found at 4-year follow-up (0.10% and 87.3%, respectively). In the context of patients with heart failure, persistent AF, and CRT, although long-term sinus rhythm maintenance may be difficult to achieve, a reduction in AF burden may be sufficient to achieve a benefit owing to improved biventricular pacing and atrioventricular synchrony. To this end, we will examine if changes in AF burden correlate with improvements in LV ejection fraction.

Any additional clinical benefit for AF ablation over AV node ablation will need to be carefully balanced against the risk of complications, recurrence rate, and need for repeat procedures. AF ablation is a longer and more invasive procedure than AV node ablation, requiring transseptal puncture and, often, transesophageal echocardiography and general anesthesia. AF ablation carries a 2%–3% risk of potentially life-threatening complications,^34^^,^^35^ while complication rates for AV node ablation are comparatively lower.^36^ In the CASTLE-AF study, repeat ablations were performed in 24.5% of patients assigned to AF ablation during the study period, with an overall recurrence rate of 50% at 60-month follow-up.^27^ It is therefore likely that a significant proportion of heart failure patients with CRT who undergo AF ablation will require multiple procedures, and may ultimately require AV node ablation owing to AF recurrence. To justify the increased risk to the patient, along with increased time and financial burden on healthcare systems, the clinical benefits for AF ablation would need to be clear and substantial. Although the cost-effectiveness of AF ablation has been debated, a recent analysis estimated a favorable incremental cost-effectiveness ratio for patients with AF and heart failure of £6438 per quality-adjusted life year within the UK National Health Service.^37^ The cost-effectiveness of AV node ablation for patients with existing CRT devices is not well studied, and results data from the RHYTHMIC study will allow assessment of this important factor, along with comparison with AF ablation.

## Conclusion

The RHYTHMIC study is a multicenter, prospective randomized controlled trial comparing AV node ablation and AF ablation for patients with heart failure and CRT who have low biventricular pacing. This is the first randomized trial to compare these 2 commonly used treatment strategies, and will help answer an important and frequently encountered clinical question. The results of the study will aid the future design of larger trials with hard morbidity and mortality endpoints, and help shape clinical decision-making for this challenging patient cohort.
